### Sample size

The sample size was calculated based on Cohen’s formula. As there are very few precedent studies that have conducted SAEM-CS similar to the present study, and because characteristics of the variables being tested are diverse, it was difficult to select and apply a single effect size. Thus, we set the effect size as 0.25 based on a medium *f*, which is one of Cohen’s criteria [32]. Accordingly, we have established the number of groups as 4, number of repetitions as 3, effect size as 0.25, significance level as 0.05, and statistical power as 0.8. Therefore, the total sample size required for a repeated measures ANOVA (taking into account interaction time with the treatment method), calculated using G*power, is 40 (10/group) [33].

Also, because the present study is an exploratory clinical trial, we determined that a total of 60 participants, 15 in each group, would be more appropriate. We based this on a previous study that recommended 12 participants per group for pilot studies that lack prior information [34] and other conditions used to determine the sample size for a pilot study [35] that gave a sample size of 12 per group, to which a drop-out rate of 25 % was applied. In order to minimize the dropout, the CRC will manage the treatment schedule of subjects.

Moreover, we considered the feasibility of the study, since participants will be patients with CI (which, as of 2014 average 46 per month) being treated at the Department of Neurology at the Chonnam National University Hospital. Considering the fact that among them, only 10–20 % will receive inpatient treatment at the Department of Rehabilitative Medicine and meet the selection criteria, it reaffirmed our estimation that 60 participants would be appropriate and feasible to achieve the study objectives. This also takes into account recruitment, study period, and drop-out possibilities.

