### Study design

This study is a prospective, outcome assessor-blinded, single-center, randomized controlled clinical trial with a 1:1:1:1 allocation ratio. This study is a pilot study to investigate the efficacy and safety of SAEM-CS, which is a newly developed treatment. This study is designed as a single-center study to overcome several procedural and organizational difficulties in terms of developing a research team, since SAEM-CS involves the simultaneous conduction of SA and rTMS. Participants (*n* = 60) who fit the inclusion and exclusion criteria will be randomly allocated into a control group (*n* = 15), SA group (*n* = 15), rTMS group (*n* = 15), and SAEM-CS group (*n* = 15). All groups will receive conventional stroke rehabilitation therapy twice/day, five times/week (excluding Saturdays and Sundays), for a total of 15 times over the course of a 3-week hospitalization period at Chonnam National University Hospital. In addition, the SA group will receive SA therapy, the rTMS group will receive rTMS therapy, and the SAEM-CS group will receive SAEM-CS therapy once/day. Outcome measures will be determined at baseline (before intervention), 3 weeks after the first intervention (end of the intervention), and 4 weeks after completion of the intervention.

This study was approved by the Ministry of Food and Drug Safety (MFDS), Medical Device Clinical Trial Plan Approval number 516. (See Additional file 1.)

The study design is summarized in Table 1 and Fig. 1.

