### Data analysis

Continuous data will be presented as means and standard deviations, while categorical data will be presented as frequencies and percentages. A repeated measures ANOVA will be conducted for the FMA and all secondary outcomes (NIHSS, MBI, FIM, K-MMSE, 9HPT, ASHA-NOMS, FAC, EQ-5D, MAS, Hand Grip Strength, and MEPs). Dependent variables include measured values before and after intervention and the measured values 4 weeks after completion of intervention. An *F* test will be conducted to detect differences between therapies, and Tukey’s post hoc test will be conducted to identify the groups. Repeated contrast tests will be conducted to account for time differences in each group, and the interaction group and time test will be conducted. A *p* value of <0.05 will be considered significant, and participants who drop out of the study will be excluded from the analysis. In brief, only complete case analyses will be used; thus, only subjects who complete the three evaluations will be analyzed. All statistical analyses will be performed using SPSS version 22.0 software (SPSS Inc., Chicago, IL, USA).

Data from participants who engage in less than 70 % of protocol adherence (i.e., receive <10 treatments from 15 trials) will be eliminated. Missing values will be implemented by multiple imputations. In addition, statistical differences will be verified by comparing attribution between eliminated and completed participants to check particular factors causing drop-out.

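### The 25% drop-out allowance was added to 12 per group instead of divided out: 15 per group keeps 12 completers only up to 20% loss

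*Protocol article*

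**What the plan says.** The Sample size section gives two routes to a number.

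- **Power route.** For a repeated measures ANOVA with a group-by-time interaction, "we have established the number of groups as 4, number of repetitions as 3", with "effect size as 0.25, significance level as 0.05, and statistical power as 0.8". The result is 40 in total, 10 per group, with no drop-out allowance mentioned.
- **Pilot route.** The section then says that "we determined that a total of 60 participants, 15 in each group, would be more appropriate". The basis is one source that "recommended 12 participants per group for pilot studies that lack prior information" and further pilot-size conditions "that gave a sample size of 12 per group, to which a drop-out rate of" 25% was applied.

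A feasibility paragraph on recruitment at the single centre is then offered as confirming 60.

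The Data analysis section excludes drop-outs and states that "only subjects who complete the three evaluations will be analyzed". It also removes patients who received fewer than 10 of the 15 treatments, and separately says that missing values will be multiply imputed.

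**The concern.** The pilot route is the one that produces the planned 60; the power route gives only 40. Its last step turns 12 into 15 by way of a 25% drop-out rate. Adding 25% to 12 gives 15, but losing 25% of 15 does not give back 12. Someone reading the section would conclude that the trial can lose a quarter of its patients and still have 12 per group to analyse. If the arithmetic is wrong, that tolerance is overstated, and the same allowance could be carried into the planning of a later trial.

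**Working it through.** **Inputs, all from the protocol article.** 12 per group, a 25% drop-out rate, and 15 per group or 60 in total (Sample size); four groups in equal allocation (Study design); complete-case analysis (Data analysis).

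**Step 1: reproduce the plan's figure.** n × (1 + d) = 12 × 1.25 = 15 per group, and 4 × 15 = 60. This matches exactly, so it is the operation that was used.

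**Step 2: the number that keeps 12 after 25% loss.** n/(1 − d) = 12/0.75 = 16 per group, and 4 × 16 = 64. The planned number is short by 1 per group, 4 in total.

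**Step 3: what 15 per group leaves.**

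| Loss | Completers per group | Total |
|---|---|---|
| 20% | 15 × 0.80 = 12 | 48 |
| 25% | 15 × 0.75 = 11.25 | 45 |

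The largest loss that still leaves 12 is 1 − 12/15 = 20%, that is, 3 of 15. At 25% the expected shortfall is 12 − 11.25 = 0.75 per group, or 48 − 45 = 3 in total.

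**Step 4: chance of keeping 12 in a given group.** Assume that each patient is lost independently with probability 0.25 (an assumption, not in the document). The binomial probability of at least 12 completers is 0.46 with 15 enrolled and 0.63 with 16.

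**Step 5: does the power route survive?** For the within-between interaction, λ = f² × N × m/(1 − ρ), df1 = (4 − 1)(3 − 1) = 6 and df2 = 2(N − 4), with f = 0.25, m = 3 and α = 0.05. The correlation ρ and the sphericity correction are not stated; I take ρ = 0.5 and sphericity.

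- N = 40: power 0.805, so the plan's 40 is reproduced.
- N = 45: power 0.860.

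The requirement is sensitive to ρ. In steps of one patient per group, 80% power needs 76 in total at ρ = 0, 56 at 0.3, 40 at 0.5 and 28 at 0.7. Of these values only 0.5 returns the plan's 40, so comparing 45 with 40 holds on the plan's own terms and not for every correlation.

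**The case against.** The strongest defence has four parts.

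- **Twelve is never called a number of completers.** The text does not say evaluable or after loss, and whether the cited pilot-size sources mean enrolled or analysed patients cannot be checked here. This stands as far as it goes: the target of 12 completers is implied, not stated. But a drop-out allowance has little purpose unless 12 are meant to remain, and the analysis is restricted to completers.
- **The 25% could be a plain surcharge on 12.** This fails. The text calls it a drop-out rate, and the section goes on to describe how drop-out will be minimised.
- **The losses may not all leave the analysis.** A reader might infer that every lost patient is removed and that patients with fewer than 10 sessions are lost on top of the 25%. The document does not settle either point. Data analysis states a complete-case rule but also mentions multiple imputation. It also compares eliminated with completed participants to look for causes of drop-out, which suggests that low-adherence patients may already be counted as drop-outs. So 45 is the expectation under the complete-case rule, and it falls further only if those patients lie outside the 25%.
- **Nothing in the trial depends on it.** This largely stands. The study is described as a pilot and as exploratory, 12 is a rule of thumb, and feasibility is given as further support for 60. That limits the importance of the error but does not make the calculation right.

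**Conclusion.** Wrong as written, minor. The 25% was applied by multiplication where division by 0.75 was needed, so 15 per group does not preserve the 12 that the step implies at the stated drop-out rate. The expected shortfall is 0.75 completers per group, 3 in total. The true tolerance is 20%, not 25%. This rests on figures in the Sample size section and on reading 12 as completers, as the complete-case rule supports.

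A reader might infer that the trial is therefore underpowered or has to enrol 64. The document does not support that. Its only power-based requirement is 40, and 45 expected completers exceed it, with interaction power of about 0.86 if the correlation is 0.5 and sphericity holds.

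**What to change.** Keep 60 and replace the drop-out statement in the Sample size section with wording such as: *15 per group leaves 12 evaluable per group at a drop-out rate of 20%; at 25%, about 11 per group (45 in total) remain.*

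This changes one sentence and leaves enrolment, analysis and endpoints as they are. The cost is that the stated drop-out tolerance becomes slightly less favourable.

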### Data monitoring

The Data Monitoring Committee (DMC) is composed of the PI and coordinators who are in charge of scalp acupuncture needles ([name], resident of the Department of Korean Medicine Rehabilitation, College of Traditional Korean Medicine, Dong-Shin University) and rTMS ([name], an occupational therapist in the Department of Physical and Rehabilitation Medicine at Chonnam National University Hospital). If needed, they will report the monitoring results to the PI. Finally, this study is independent from any sponsors.

### Data analysis

Continuous data will be presented as means and standard deviations, while categorical data will be presented as frequencies and percentages. A repeated measures ANOVA will be conducted for the FMA and all secondary outcomes (NIHSS, MBI, FIM, K-MMSE, 9HPT, ASHA-NOMS, FAC, EQ-5D, MAS, Hand Grip Strength, and MEPs). Dependent variables include measured values before and after intervention and the measured values 4 weeks after completion of intervention. An *F* test will be conducted to detect differences between therapies, and Tukey’s post hoc test will be conducted to identify the groups. Repeated contrast tests will be conducted to account for time differences in each group, and the interaction group and time test will be conducted. A *p* value of <0.05 will be considered significant, and participants who drop out of the study will be excluded from the analysis. In brief, only complete case analyses will be used; thus, only subjects who complete the three evaluations will be analyzed. All statistical analyses will be performed using SPSS version 22.0 software (SPSS Inc., Chicago, IL, USA).

Data from participants who engage in less than 70 % of protocol adherence (i.e., receive <10 treatments from 15 trials) will be eliminated. Missing values will be implemented by multiple imputations. In addition, statistical differences will be verified by comparing attribution between eliminated and completed participants to check particular factors causing drop-out.

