### Randomization

After signed informed consent and baseline measurements are obtained, random allocation software (developed by M. Saghaei, M.D., at the Department of Anesthesia, Isfahan University of Medical Sciences, Isfahan, Iran) is used to assign a serial number to the 60 research volunteers and to randomly allocate 15 of them into each group. The serial number codes will be inserted into sealed, opaque envelopes, kept in a double-locked cabinet, and opened in the presence of the patient and a guardian.

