### Outcome measurements

Primary and secondary outcome assessments will be conducted at baseline (before intervention), 3 weeks after the first intervention, and 4 weeks after completion of intervention.

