### Secondary outcomes

Secondary outcome measures will be assessed changes in the National Institutes of Health Stroke Scale (NIHSS) score, Modified Barthel Index (MBI), Functional Independence Measurement (FIM) score, Korean Mini-Mental State Examination (K-MMSE) score, American Speech-Language-Hearing Association National Outcomes Measurement System (ASHA-NOMS) Swallowing Scale score, Functional Ambulation Categories (FAC), European Quality of Life-5 Dimensions (EQ-5D), Modified Ashworth Scale (MAS) score, Hand Grip Strength Test, MEPs, mRS score, and 9-Hole Peg Test (9HPT).

The NIHSS is a scale that was developed by the United States National Institutes of Health, and provides useful information on the severity, prognosis, and early treatment of stroke [9].

The MBI is an assessment tool used to objectively evaluate performance of everyday movements on 10 items: personal hygiene, bathing, eating, toilet use, ability to climb stairs, ability to dress, bowel/bladder function, walking function, capability of getting into and out of a chair/bed, and mobility [21].

The FIM is an assessment of everyday movement performance that evaluates 13 detailed items of motor FIM and 5 detailed items of cognitive FIM. The FIM has a total possible score of 18–126, and each item is divided into seven stages, allowing for a comparably detailed assessment. Higher FIM scores indicate higher functional independence [22].

The MMSE is a brief global instrument used to assess cognitive abilities and has been translated into Korean (K-MMSE) [23]. The K-MMSE is a quick screening assessment tool that was developed to evaluate cognitive function and dementia in elderly patients with suspected dementia or patients with brain damage. The instrument consists of measures used to assess orientation, recall, attention and calculation, language, judgment, and understanding. A score ≥24 points indicates definitive normal, 20–23 indicates suspected dementia, and ≤19 indicates definitive dementia [24].

The ASHA-NOMS is a seven-stage dysphagia scale developed by the American Speech-Language-Hearing Association to evaluate severity of dysphagia for items such as parenteral hyperalimentation, whether independent eating is possible, use of compensative skills for eating, and diet limitations [25].

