The FAC is designed to evaluate walking ability where a patient’s independent walking ability is categorized into six ranks: 0 = unable to walk, 1 = direct assistance required by the therapist, 2 = intermittent and direct assistance required by the therapist, 3 = able to walk independently but requires observation, 4 = able to walk independently but requires assistance on uneven surfaces, and 5 = able to independently walk on even surfaces [26].

The EQ-5D evaluates quality of life in five fields including exercise ability, self-management, daily activities, pain/discomfort, and anxiety/depression. Each field is divided into three levels with 1 indicating a good state of health. The EQ-5D also includes a visual analog scale in which a subject indicates subjective and overall individual health status on a vertical scale where the best health state is 100 points and the poorest health state is 0 points [27].

The MAS assesses muscles by measuring spasticity in the wrist and elbow joints while the joints are maximally bent. Scores range from 0, where there is no increase in muscle tone, to 4, where there is contracture in bent and straight muscles and/or joints [15].

The Hand Grip Strength Test evaluates muscle strength in the hands and is conducted twice in six stages; the higher value (kg) of the two tests is recorded [9].

In the current study, MEPs are evoked by stimulating the primary motor cortex on representation of hand grip muscles without pain, and responses of the FDI muscle are then observed. MEPs are useful to predict functional recovery in CI. Here, the cerebral hemisphere is magnetically stimulated in a figure 8 shape while the patient is lying down. Stimulations increase in intensity from 0 to 100 % until the MEP with the shortest latency occurs. The latency and the amplitude of the MEP responses are recorded [28].

The mRS is a six-point, ordinal hierarchical scale that describes “global disability” with a focus on mobility. The mRS is often used in contemporary stroke studies as a measure of premorbid ability and is used to assist in the selection of patients and as a final outcome measure. The mRS uses a 5-min non-standardized interview, and has six potential scores (0–5), which describe a full range of stroke outcomes; a score of 6 denotes death [29, 30].

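### Baseline MEP response, which the protocol itself calls predictive of recovery, is left out of the primary FMA model; one pre-specified covariate could recover some precision at almost no cost

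*Protocol article*

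**What the plan says.** The Data analysis section of the protocol article fixes the primary model: "A repeated measures ANOVA will be conducted for the FMA and all secondary outcomes". The tests named are a between-therapy F test with Tukey's post hoc comparisons, repeated contrasts over time, and the group-by-time interaction. No baseline covariate is named, and MEP appears only as a further dependent variable.

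Under Secondary outcomes, the paragraph on MEPs says that "MEPs are useful to predict functional recovery in CI". It records latency and amplitude of the response in the first dorsal interosseous (FDI) muscle. It does not say which hemisphere or hand is tested. The same section credits the NIHSS with information on prognosis.

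Both measures are available before treatment is assigned. The Outcome measurements section gives the timing as follows: "Primary and secondary outcome assessments will be conducted at baseline (before intervention), 3 weeks after the first intervention, and 4 weeks after completion of intervention". Under Randomization the order is "After signed informed consent and baseline measurements are obtained, random allocation software" and then assignment. The software is to "randomly allocate 15 of them into each group", and no stratification factor is mentioned.

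**The concern.** The article names a predictor of recovery and collects it before randomisation, then leaves it out of the model for recovery. Two things follow. Variation in FMA change that baseline MEP could explain stays in the residual, which widens every arm comparison. And with 15 patients per arm and unstratified allocation, arms can differ by chance in MEP response, with nothing in the model to account for it. The objective is to compare SAEM-CS with each of three other arms, so these are small-sample contrasts in which precision is scarce.

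**Working it through.** **Inputs from the article (Sample size section).** Four groups (k = 4), three repetitions (m = 3), f = 0.25, alpha 0.05, power 0.80, stated total 40. The enrolled total is 60, from 12 per group with a 25% drop-out allowance. Since 12 × 1.25 = 15, the intended number of completers is 4 × 12 = 48.

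**Assumed inputs (not in the article).** Correlation among repeated measures ρ = 0.5; sphericity; correlation r between baseline MEP and FMA change of 0.1 to 0.5, the same for both time contrasts; share of patients without an MEP of 10%, 20% or 40%.

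**Formula.** For the group-by-time test, non-central F with λ = f² × N × m / [(1 − ρ)(1 − r²)], df1 = (k − 1)(m − 1) = 6 and df2 = (m − 1)(N − k − c). Here c = 0 without the covariate and c = 1 with it.

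**The plan's own figure.** N = 40, r = 0: λ = 0.0625 × 40 × 3 / 0.5 = 15.0, df2 = 72, power 80.5%. N = 36 gives 74.9%. The stated total of 40 therefore reproduces under ρ = 0.5.

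**At 48 completers.** Unadjusted: λ = 0.0625 × 48 × 3 / 0.5 = 18.0, df2 = 88, power 88.7%. With the covariate, df2 = 86:

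| r | λ | Power | Gain (points) |
|---|---|---|---|
| 0 | 18.0 | 88.6% | −0.1 |
| 0.1 | 18.2 | 89.0% | 0.3 |
| 0.2 | 18.8 | 90.0% | 1.3 |
| 0.3 | 19.8 | 91.7% | 3.0 |
| 0.4 | 21.4 | 93.9% | 5.2 |
| 0.5 | 24.0 | 96.3% | 7.6 |

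(Gains are differences of the rounded powers.)

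**Other completer counts.** If 25% of the 60 are lost (45 remain), power is 86.0% unadjusted, 89.5% at r = 0.3, and 85.9% if MEP is unrelated. With all 60, it is 95.4% unadjusted and 99.1% at r = 0.5.

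**Chance imbalance.** With K MEP-absent patients among 60, the chance that two given arms of 15 hold a and b of them is C(15,a) × C(15,b) × C(30, K − a − b) / C(60, K). Summing over differences of 3 or more patients gives:

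| Share MEP-absent | K | Two given arms differ by ≥ 3 |
|---|---|---|
| 10% | 6 | 0.13 |
| 20% | 12 | 0.26 |
| 40% | 24 | 0.36 |

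**What an imbalance does.** For a standardised covariate, the 95% range of the difference between two arms of 15 is ±1.96 × √(2/15) = ±0.72 SD. An imbalance at that limit moves the unadjusted difference in FMA change by r × 0.72: 0.07 SD at r = 0.1 and 0.36 SD at r = 0.5.

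**The case against.** The case for leaving the model alone has real weight.

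- **Covariates are often left to an analysis plan.** This is true, and a condensed article need not list everything. But this one sets out the primary model and bases its sample-size calculation on a repeated measures ANOVA. The suggestion is an addition to that stated choice; it does not complain that something is missing.
- **Randomisation already protects the comparison.** A reader might infer that the unadjusted FMA comparison is biased. It is not: over all randomisations the test holds its 5% level, and the point concerns precision and the particular imbalance that one trial may draw.
- **The document does not single out patients without an MEP.** A reader might infer that, by the article's own account, patients with no MEP in the affected hand recover differently. The article does not say this. It gives a general predictive statement, names no tested side for the outcome measurement, and mentions no present/absent coding. The only limb it names for FDI responses is the unaffected one, for locating the rTMS hot spot.
- **MEP is not the only candidate.** The NIHSS is also described as prognostic and is also measured at baseline, so it is equally eligible.
- **Baseline FMA is already a level of the outcome.** The group-by-time test therefore removes whatever MEP shares with baseline FMA. Only the part related to change remains to be gained.
- **The power target is met anyway.** On the plan's effect size with ρ = 0.5, 48 completers give 88.7% without any covariate, and at r = 0.1 or 0.2 the gain is at most 1.3 points.

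These objections limit the point to an optional gain of unknown size. They do not show any material cost to taking it.

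**Conclusion.** The point holds as a modest one about efficiency. The article calls MEPs predictive, measures them before allocation and does not use them in the FMA model. The gain at 48 completers runs from 0.3 to 7.6 points of group-by-time power for r of 0.1 to 0.5, against a loss of about 0.1 point if MEP is unrelated. The probability that two given arms differ by 3 or more MEP-absent patients runs from about 0.13 to 0.36 for absent shares of 10% to 40%. These ranges rest on assumed values of r and of the MEP-absent share, and the power figures also on ρ = 0.5; the article supplies none of the three. The stated total of 40 should not be read as wrong on this account: it reproduces under ρ = 0.5. For a trial that describes itself as a pilot and exploratory, this is a low-cost suggestion.

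**What to change.** In the Data analysis section, before outcomes are seen, pre-specify baseline MEP response, with its interaction with time, as a covariate in the primary FMA model. State the side (affected FDI) and the coding, for example present or absent, which gives every tested patient a value even when latency cannot be measured. Confirm that the affected side is recorded at baseline in every patient. If it is not, use baseline NIHSS as the single covariate instead. The choice should not be made after an imbalance has been observed, because the adjustment would then be post hoc.

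The cost is one added line and one between-subject degree of freedom, using measurements already planned. Visits, allocation, treatment and sample size are unchanged.

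### The list of analysed secondary outcomes claims to be complete but omits the mRS, and the complete-case rule would discard deaths that the mRS scores

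*Protocol article*

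**What the plan says.** The Secondary outcomes section opens its list with "Secondary outcome measures will be assessed changes in the National Institutes of Health Stroke Scale (NIHSS) score, Modified Barthel Index (MBI" and closes it with "Hand Grip Strength Test, MEPs, mRS score, and 9-Hole Peg Test (9HPT". The mRS is thus a declared secondary outcome. The same section describes it: "The mRS is a six-point, ordinal hierarchical scale", scored 0 to 5 in the living, and "a score of 6 denotes death". It adds that the scale is used as a final outcome measure in stroke studies.

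The Data analysis section states: "A repeated measures ANOVA will be conducted for the FMA and all secondary outcomes". The bracket attached to that sentence reads in full: "all secondary outcomes (NIHSS, MBI, FIM, K-MMSE, 9HPT, ASHA-NOMS, FAC, EQ-5D, MAS, Hand Grip Strength, and MEPs". Its last six entries are "ASHA-NOMS, FAC, EQ-5D, MAS, Hand Grip Strength, and MEPs". The mRS is not in it, and no other sentence in the article names an analysis for the mRS.

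The same section restricts the analysis to patients with all three evaluations and removes those who received fewer than 10 of the 15 treatments. It also says that missing values will be multiply imputed.

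**The concern.** A list that calls itself complete and is not complete gives two answers to one question. An analyst who wants to report global disability can rely on the general phrase; one who does not can rely on the bracket. The trial has four arms, twelve secondary outcomes, and participants and practitioners who know the treatment, so that choice should be closed before outcome data are seen.

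Adding the abbreviation to the bracket would not settle the matter. It would bring the mRS under the complete-case rule. For most scales a patient who has died has no value. For the mRS, as this article describes it, death is a value, and the worst one. Excluding such a patient as incomplete discards a known outcome and can make an arm look better than it was.

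**Working it through.** **Step 1. Compare the two lists.**

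- Secondary outcomes section: NIHSS, MBI, FIM, K-MMSE, ASHA-NOMS, FAC, EQ-5D, MAS, hand grip strength, MEPs, mRS, 9HPT. Count: 12.
- Data analysis section, bracket: NIHSS, MBI, FIM, K-MMSE, 9HPT, ASHA-NOMS, FAC, EQ-5D, MAS, hand grip strength, MEPs. Count: 11.
- In the first list and not in the second: mRS only (12 − 11 = 1).
- In the second list and not in the first: none.

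**Step 2. Follow each reading of the Data analysis sentence.**

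- If the bracket governs, the mRS is collected at three visits without a planned comparison.
- If the general phrase governs, the mRS is analysed by repeated measures ANOVA in complete cases.

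The article does not say which reading applies.

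**Step 3. Follow a death through the second reading.** Evaluations take place at baseline, at 3 weeks and 4 weeks after treatment ends, about 3 + 4 = 7 weeks in all.

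- Death during treatment: the patient lacks the second and third evaluations and is dropped. If fewer than 10 treatments were given, the adherence rule also removes the patient. The mRS would be 6 at both post-baseline times.
- Death between the end of treatment and follow-up: the patient lacks the third evaluation and is dropped, so the measured end-of-treatment value is lost too. The mRS at follow-up would be 6.
- Multiple imputation does not repair this. It fills in unknown values, and here the value is known. The article's imputation sentence also conflicts with its own complete-case rule.

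None of the other eleven outcome descriptions includes a level for death.

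**Step 4. Size.** One death in an arm of 15 is 1/15 = 6.7% of that arm. This is an illustration of scale; the article gives no mortality figure.

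**Step 5. What is not affected.** The sample-size figure of 40 (10 per group) rests on four groups, three repetitions, f = 0.25, alpha 0.05 and power 0.8. It reproduces from the noncentral F distribution for the group-by-time interaction: noncentrality = f² × N × m/(1 − ρ) = 0.0625 × 40 × 3/0.5 = 15, with (4 − 1)(3 − 1) = 6 and (40 − 4)(3 − 1) = 72 degrees of freedom, giving power 0.805. The correlation of 0.5 and sphericity are assumptions, since the article states neither. The mRS does not enter this calculation.

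**The case against.** The strongest reply is that the sentence already covers the mRS. It speaks of all secondary outcomes, and the mRS is one of them, so the bracket is probably a drafting slip. This stands in part. A reader might infer from the bracket that the mRS has no stated analysis, or is collected and deliberately left unanalysed. The article does not support that: the general phrase includes the mRS, and the scale is openly declared as an outcome. What remains is a contradiction between the phrase and its own list.

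A second reply is that the argument about deaths is hypothetical. Patients are judged stable by a neurologist, enter with an mRS of 2 to 4 and are followed for about seven weeks. Death is not among the expected adverse events, and the line about level 6 reads as a general description of the scale. This limits the size of the point, and no claim that deaths are expected can be drawn from the article. The loss of 1/15 is also the same for any dropout, and the complete-case rule affects every outcome. The difference for the mRS is that a death leaves an observed value there, and the stated rule would discard it.

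A reader might also extend the point to the other short ordinal scales and conclude that ANOVA is wrong for FAC ("independent walking ability is categorized into six ranks"), MAS and ASHA-NOMS. That goes further than can be shown. These are secondary outcomes in an exploratory pilot, and nothing in the article points to a distorted error rate or a bias. Simulated null data on five- and six-level scales, with assumed level distributions, an assumed latent correlation of 0.6 and 12 or 15 patients per arm, kept the error rate of the group-by-time test near its nominal 5%. Those assumptions do not prove the general case, but short scales alone do not invalidate the test. Replacing it would give up the planned interaction test and meet sparse levels at 15 per arm.

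**Conclusion.** The contradiction is established by comparing the two lists: twelve outcomes are declared, eleven are listed for analysis, and the mRS is the one missing. It leaves room for selective reporting of global disability. If the general phrase is taken to include the mRS, the complete-case rule would exclude any patient who dies, although the article gives death its own mRS level. This consequence follows from the stated rules and needs no assumption about how many deaths occur; its practical size does depend on that number, which the article does not give.

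Severity is minor. One secondary outcome is affected, and the primary FMA analysis and the sample size stand as they are. The point does not extend to the analysis of FAC, MAS or ASHA-NOMS.

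**What to change.** In the Data analysis section:

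1. Add the mRS to the bracketed list, so that it matches the Secondary outcomes section.
2. State separately that the mRS is compared between the randomised groups at the end of treatment and at 4 weeks after treatment with an ordinal or rank-based method that accounts for baseline mRS. Two candidates are a proportional-odds model adjusted for baseline mRS and a rank test stratified by it; entry criteria allow three baseline levels, 2 to 4.
3. State that a patient who has died is kept at level 6 and is not excluded as an incomplete case.

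Patients who are alive but lack an mRS value fall under the general missing-data rule, once the complete-case and multiple-imputation sentences have been reconciled.

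The cost is wording only: no new data, visits or patients. The downside is that the mRS result is reported on a different scale from the other outcomes. With 15 patients per arm, sparse levels may limit a proportional-odds model, which favours choosing the rank-based form or fixing a rule for merging levels in advance.
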